### CHARM intervention overview

As noted above, CHARM involved three gender, culture and contextually-tailored family planning and gender equity counseling sessions delivered by trained village health care physicians (VHPs) to men (Sessions 1&2) and couples (Session 3) in a clinical setting, or if required, near or in the home of the participant. (Curriculum available upon request.) The intervention was designed to allow Sessions 2 and 3 to be optional, such that all key information was delivered to the male participant in the first session but extended and reinforced in the subsequent sessions. A desk-sized CHARM flipchart provided pictorial information on family planning options, barriers to family planning use, including gender equity-related issues and the importance of healthy and shared family planning decision-making, to be used by VHPs during male one-on-one and couple-based sessions. VHPs were selected to include private as well as public practitioners, based on private VHPs’ greater availability in the villages. This approach of using VHPs was based on the premise of extending public health services (e.g., family planning supervision/training and contraception options) via the private VHPs, in order to support public-private partnerships for family planning delivery so that learnings would be useful for the national program. As most private VHPs are male, the CHARM intervention was designed to involve men reaching men to improve family planning, and simultaneously, offers more local family planning access. Sessions were to be clinic-based, but near or at home sessions were offered; 59.1 % (n/n = 205/469) of CHARM participants received at least one session at home. All sessions included provision of FP + GE counseling and services. The role of VHPs was to assess and communicate with participants on family planning for a maximum of three sessions (if men expressed interest), provide condoms (to those men who expressed interest), and provide oral contraceptive pills if the couple or the woman presents to the VHP and expressed an interest. The VHPs’ role also included providing a referral to the public health centers for utilization of other contraceptive methods. The private VHPs under the CHARM study were paid an amount of 50 Indian rupees (approximately US$ 0.75) per CHARM session provided to a participant, as compensation for their time and services.

#### Theoretical framework

The CHARM intervention was built on Social Cognitive Theory (SCT) [34] and Theory of Gender and Power (TGP) [35]. SCT is a commonly used theory for effective family planning interventions [36] and posits that improvements in behavior, in this case contraception use, are more likely if a couple perceives positive outcomes for engaging in the behavior (e.g., birth spacing will produce healthier children), feel capable of engaging in and controlling the behavior (e.g., contraceptive knowledge and skills building), and have an environment supportive of the behavior (e.g., access to services) [34]. TGP is a social-structural theory that recognizes the role of power dynamics inherent to many heterosexual dyadic relationships advantaging men over women with regard to sexual and reproductive decision-making and economic and mobility control over issues like contraception acquisition, and use of violence and support from families and communities to maintain that control [35].

### Phase 2: CHARM evaluation (years 2–5 of study)

#### Evaluation study design

Evaluation of CHARM involved a two-armed cluster randomized controlled trial design comparing participants receiving CHARM (VHP-delivered FP + GE over 3 sessions) to those receiving standard of care public health supported family planning services. For outcome evaluation purposes, survey assessments were conducted at baseline and 9&18 month follow-ups with eligible men and their wives, and pregnancy tests were obtained from wives at baseline and 18-month follow-up (See Fig. 2). Impact on spacing contraceptive use and pregnancy were evaluated. [*Unmet need was an original outcome of the study, but standard definitions of this measure changed, and the measures we had included in this study did not allow for standard measurement of this outcome.*] To provide additional in-depth understanding of how the intervention produced any impact observed, VHPs and a subsample of couples (*n* = 50, 2 couples per intervention cluster) participated in in-depth interviews at 18 month follow-up. A process evaluation was also conducted to obtain feedback from husbands, wives and VHPs on their response to the program and fidelity to design, i.e., the extent to which the program elements were implemented according to curriculum protocols, the former based on interviews and latter based on review of clinical records.

**Fig. 2 Fig2:**

Outcome evaluation study design

#### Random assignment of clusters and cluster preparation for study

Using computer-generated random numbers, clusters selected in the community mapping procedure described previously were randomized by our research team to either intervention or control conditions. Random allocation of clusters into intervention and control conditions group was done on 20th Feb 2012 at 2:05 PM. A schedule was then created to roll out the study for recruitment over a one year period, on a rolling basis. In the month prior to roll out of the study in each selected cluster, intervention and control, the study team met with key providers and leaders in that community to provide a more supportive infrastructure for study implementation. Group meetings were held that involved village panchayat leaders (recognized and respected community elders serving as village leaders), ASHAs (community health outreach workers) and other village-level public health workers (auxiliary nurse midwives—ANMs) to discuss the project and how it will be implemented. ASHAs were also engaged to connect to CHARM VHPS and to provide linkage to CHARM couples for public health family planning services, when requested.

#### Participants and eligibility criteria

Primary study participants for intervention evaluation were rural young men and their wives. Inclusion and exclusion criteria are identified in Table 1, below.

**Table 1 Tab1:** Criteria for participation of couples

Inclusion criteria	Exclusion criteria
Age 18–30 years and Fluent in Marathi	Cognitive Impairment (husband or wife)
Willing to Have Wife Included in the Study	Sterile or Wife is Sterile
Residing in the village for the past 2 years and residing with wife in village for past 3 months	Intend to move in next 18 months or either spouse refuses participation

Surveys were administered at baseline and 9&18 month follow-ups, pregnancy tests were taken at baseline and 18 month follow-up to determine program impact on key outcomes (spacing contraceptive use, communication). A subsample of CHARM couples (*n* = 50, 2 couples per CHARM intervention cluster) participated in in-depth interviews at 18 month follow-up to assess how the program affected their relationship and behaviors. Male CHARM participants also completed a brief survey on their perceptions of the program. Qualitative data were also collected from CHARM VHPs regarding their views of the program at study completion to provide VHP perceptions on how the intervention impacted family planning behaviors. Between March 2012 and December 2012, 1,881 couples were screened and 1,043 were determined to be eligible to participate in the study. Of those identified as eligible, 1,081 couples were enrolled into CHARM and completed a baseline survey. A log was maintained to track eligibility, participation and enrollment rates by cluster and treatment group, reasons for refusal among the eligible, and dates of approach and screening. These were reviewed on weekly calls to track the recruitment and enrollment process for quality and scheduling purposes, and make course corrections as needed.

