**Fig. 3 Fig3:**
[figure not shown]
Consort flowchart

Due to the nature of the intervention and study design, neither the study subjects nor the research and program staff were blinded. However, the study was designed to minimize measurement bias. Additionally, all research interviewers were trained on the importance of uniform interview procedures. Drs. [name], [name] and [name] were responsible for the training and supervision of these research interview staff.

Qualitative data was collected from a subsample of intervention couples (*n* = 50 couples) and CHARM-trained VHPs (*n* = 16 VHPs) who conducted any sessions, in order to provide further insight into outcome findings. At 18 month follow-ups, 2 randomly selected participating couples from each intervention village (*n* = 50 couples total) were asked to participate in in-depth interviews. The interviews were jointly conducted by the NIRRH team of 1 male and 1 female who also conducted the survey separately with the couple. Only couples who participated in all 3 sessions (including wives in session 3) were eligible for qualitative interview participation, biasing the perspectives on the intervention but allowing for insight into the utility of the full program. The in-depth interview guideline for couples assessed respondents’ perceptions of how their relationship and family planning practices changed since participating in the program and how the intervention created or affected these changes. Interviews were 45–60 min in length and conducted in Marathi. CHARM-trained VHPs who delivered sessions (*n* = 16) also participated in in-depth interviews subsequent to study completion. The 30 min open-ended interviews with intervention VHPs assessed their perceptions of how CHARM affected the couples with whom they met and whether behavior changes and ongoing contact for family planning services continue subsequent to the intervention. They were also asked about the strengths and weaknesses of the program. Data were collected and analyzed using the same methods as described above for formative research.

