Intervention participants also completed a brief survey at follow-up on their experiences with the intervention, including FP content covered in sessions, delivery of contraceptives, perceptions of the strengths of the VHPs, perceptions of the utility of the men-only and couple sessions, and recommendations for the program. This was part of the process evaluation component to assess quality of delivery and response to program. A weakness of this assessment was lack of measures focused on GE elements of the intervention. For the participant satisfaction surveys, most men assigned to receive CHARM also provided survey responses (84.9 %; n/n = 398/469). Most responders (87.2 %; n/n = 347/398) had participated in CHARM and were able to provide feedback on their experiences of intervention delivery

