#### Analytic plan

Outcome analyses were designed to focus on the following outcomes of interest: spacing contraceptive use and communication, and included pregnancy, intimate partner violence and attitude outcomes based on women’s reports and pregnancy testing. The primary comparison of the outcomes by treatment group at 9 and 18 month follow-ups were done using mixed-effects regression models, with a nested random effects structure for the geographical clusters and for each couple within the cluster, over time. The treatment effect was evaluated via a time-by-treatment arm interaction. A categorical time effect was used (profile model). This treatment effect can be interpreted as the individual-level effect of the intervention. In addition, generalized estimating equations (GEE) logistic regression models with the same clustering and mean model structure and exchangeable working correlation matrix was used to express the intervention effect at the population level. Secondary analyses adjusted for relevant covariates to improve precision and possibly reduce bias. Demographic and fertility variables (e.g., age, current pregnancy, past year childbirth, etc.) were considered for inclusion in adjusted analyses, in addition to time and treatment arm, using backward model selection at the 0.15 threshold level. Bivariate analyses were conducted to assess differences in demographics, fertility history, and outcomes at baseline: 1) by treatment group, 2) for those lost to study follow-up, and 3) for CHARM participants lost to intervention. Any characteristics identified as significantly different between groups were considered as potential covariates in these adjusted models. Outcome analyses used an intent-to-treat approach and analyzed all subjects according to randomized group. Additional analyses were conducted based on receipt of intervention. All analyses used women’s data only, but men’s data will be used to validate findings on contraceptive behavior outcomes. All analyses were conducted using SAS (SAS Institute, Version 9.4, Cary, NC, USA).

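### The recruitment flow is impossible as printed (1,081 enrolled of 1,043 eligible), and couples were recruited unblinded after allocation while covariate adjustment is secondary and chosen by significance

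*Protocol article*

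**What the plan says.** On recruitment, the section on participants and eligibility criteria says that, of 1,881 couples screened from March to December 2012, "1,043 were determined to be eligible to participate in the study. Of those identified as eligible, 1,081 couples were enrolled into CHARM". It also says that a log of eligibility, participation and enrolment by cluster and treatment group was kept, with reasons for refusal.

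On timing, the section on random assignment of clusters says: "Random allocation of clusters into intervention and control conditions group was done on 20th Feb 2012 at 2:05 PM". On blinding, the text after the CONSORT flowchart (Fig. 3) says that "neither the study subjects nor the research and program staff were blinded".

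On arm size, the section on quantitative measures reports that "most men assigned to receive CHARM also provided survey responses", with 84.9 % given as 398/469. The CHARM intervention overview prints 59.1 % beside "n/n = 205/469) of CHARM participants received at least one session at home". The sample size section assumed 1,000 couples, equal arms and 20 men per cluster.

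On analysis, the analytic plan makes a mixed-effects model the primary comparison, with the treatment effect read from a time-by-arm interaction and time as a category. Covariates come later: "Secondary analyses adjusted for relevant covariates to improve precision and possibly reduce bias". They are chosen by backward selection with a 0.15 cut-off. Characteristics that differ significantly at baseline are among the candidates.

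**The concern.** Randomising clusters balances the populations of the clusters. It does not balance the couples who enrol after the allocation is known to the people recruiting them. In such a design, the counts of screened, eligible, refusing and enrolled couples by arm are the main evidence on whether uptake differed. Here the one published set of counts is impossible, so no uptake rate can be calculated from it. The apparent arm sizes differ by 30 % where equal arms were planned, and the article's text does not explain the difference.

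If recruits did differ between arms, the analysis would need to protect the treatment effect. The factors most likely to drive contraceptive uptake or pregnancy over 18 months are left to secondary models, and which of them are kept depends on significance tests in the same data.

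**Working it through.** **1. Flow.** Inputs: 1,881 screened, 1,043 eligible and 1,081 enrolled (participants section). 1,081/1,043 = 103.6 %, and 1,081 − 1,043 = 38. To see which number is likelier wrong, take the follow-up counts in the procedure section:
- With 1,081 as denominator, 898/1,081 = 83.1 % and 891/1,081 = 82.4 %, both as printed.
- With 1,043, the results would be 86.1 % and 85.4 %.

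The article uses 1,081 consistently, so the eligible count is the likelier error. Its true value cannot be derived, but it must be at least 1,081 if the enrolled count is right.

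**2. Home sessions.** 205/469 = 43.7 %. 205/347 = 59.1 %, and 347 is the number of satisfaction-survey responders who had taken part in CHARM (quantitative measures).

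**3. Arm sizes.** 398/469 = 84.9 %, as printed. The session percentages in the procedure section (91.3 %, 77.2 %, 52.5 %) also fit 469, as 428, 362 and 246 couples. Control = 1,081 − 469 = 612, and 612/469 = 1.30. With 25 clusters per arm, 469/25 = 18.8 and 612/25 = 24.5, against 20 planned. The gap is 24.48 − 18.76 = 5.72 couples per cluster.

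**4. Is the gap more than chance?** The cluster is the unit that was allocated, so t = 5.72/(SD × √(2/25)) on 48 degrees of freedom. The SD of enrolment between clusters is not reported, so a range is assumed:

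| Assumed SD | t | p |
|---|---|---|
| 5 | 4.04 | 0.0002 |
| 8 | 2.53 | 0.015 |
| 10 | 2.02 | 0.049 |
| 15 | 1.35 | 0.18 |

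**5. Power.** The plan's own figure first: 400/2.9 = 137.9 effective subjects per arm. At 10 % v 22 % this gives 77.9 % power, or 79.9 % with the printed odds ratio of 2.59 (22.35 %), so the stated 80 % is reproduced within about two points. With 469 and 612 couples, 82.4 % retained in both arms (assumed equal) and a within-cluster correlation of 0.10:
- intervention: 386.5/(1 + 0.1 × 17.76) = 139.2 effective subjects
- control: 504.3/(1 + 0.1 × 23.48) = 150.6 effective subjects

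Power at 10 % v 22 % is then 80.0 %. The unequal split does not cost the planned power.

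**6. What the primary contrast removes.** Suppose the outcome is 10 % in control and 15 % in intervention at baseline, with the same change on the logit scale in both arms. The follow-up odds ratio is (0.15/0.85)/(0.10/0.90) = 1.59, but the interaction odds ratio is 1.00. A difference in level is removed.

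**7. What it leaves.** Assume one stratum moves from 10 % to 25 % and the rest from 10 % to 12 %, with no treatment effect. If the control arm has 50 % in the faster stratum, its follow-up rate is 0.25 × 0.50 + 0.12 × 0.50 = 18.5 %. For the intervention arm:
- 55 % share: 19.15 %, interaction odds ratio 1.04
- 60 % share: 19.8 %, odds ratio 1.09
- 70 % share: 21.1 %, odds ratio 1.18

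Within each stratum the arms move identically, so a model with stratum-by-time terms returns 1.00. A main effect for stratum alone leaves the bias in place here, because the strata start at the same level.

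**The case against.** A reader might infer from 469 v 612 that recruitment was biased. The documents do not support that. The 612 is obtained by subtraction, and the CONSORT figure is not shown. Clusters were mapped to about 300 households or 1,000 people, not to equal numbers of eligible couples, so yields could differ without any selection. The gap is unremarkable if cluster enrolment varied with an SD near 15. The impossible eligible count is not split by arm, so it is no evidence of differential uptake either way.

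There are also safeguards. Intervention men were told of CHARM only after their baseline survey, preparatory meetings were held in both arms, and no incentive was paid. This limits self-selection by couples, though not selection by staff who knew the allocation.

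A reader might also infer that the primary test has no protection at all. That is wrong: a time-by-arm interaction with baseline as a time point removes differences in the baseline outcome, and adding that outcome as a covariate would use it twice. No covariate model can remove selection on unmeasured factors. Finally, the study is complete and the analyses are reported as done, so changing the primary model now would be a post hoc choice.

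Most of this stands, and it reduces the bias argument to a qualified risk. It does not touch the two wrong figures, nor the choice of covariates by significance.

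**Conclusion.** Two printed figures are wrong beyond dispute: the eligible count (enrolment at 103.6 % of it) and the home-session percentage for its denominator (43.7 %, not 59.1 %).

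Differential recruitment is a possible risk that the design left open and the published counts cannot exclude. It is not demonstrated. Its remaining route into the primary result is imbalance in factors that drive change. The size shown, a null odds ratio of 1.04 to 1.18, rests on assumed strata and shares. The conclusion that level differences are removed assumes that baseline is the reference time, which is the natural reading of the analytic plan but is not stated there. Power is not the issue.

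**What to change.** 1. Correct the eligible count and the 205/469 denominator or its percentage.
2. From the log already kept, report screened, eligible, refused and enrolled couples by arm and by cluster. Keep refusals separate from other exclusions, because the eligibility table lists refusal by either spouse as an exclusion.
3. Replace the selection-based adjusted model with one that uses a fixed set of baseline covariates already collected (age, parity, current pregnancy, past-year childbirth) inside the same longitudinal model. Let them act on change through covariate-by-time terms. Do not add the baseline outcome again; for the pregnancy outcome this means leaving baseline pregnancy off the list.
4. Present this model as primary or, because the analyses are already done, as the key sensitivity analysis beside the unadjusted model.

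The cost is a tabulation and one further model per outcome. Any change of primary model must be declared as post hoc.

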#### Procedure

Immediately subsequent to household screening and recruitment, eligible husbands and their wives were asked by trained Masters-level research staff to participate in the baseline survey (measures detailed below). Immediately subsequent to obtaining written informed consent, the survey was administered on paper for each spouse separately in a private location, by a gender-matched NIRRH staff member. Following the women’s survey, women were asked to take a urine pregnancy test under the direction of the research staff member. Test results were available within three minutes of testing and were noted by the interviewer on the woman’s survey. The interviewer confirmed the test results with the women and provided information on local antenatal services as well as family planning services at the PHC, as appropriate. Husbands were not notified of wives’ pregnancy testing or test results. After the men’s baseline survey, males in the intervention condition were notified that family planning counseling is now available in the village via trained VHPs as part of CHARM, and supported referral (i.e., direct linkage and transport if needed) to the VHP was provided. Participants were reminded that additional data would be collected from them in 9&18 months. Research staff followed up with both VHPs and men to ensure linkage occurred and to track sessions delivered. Women from both intervention and control conditions were provided subsequent to baseline survey detailed information regarding public health FP services, and linked to community health outreach workers (ASHAs) if requested. No monetary incentive was provided for study or program participation.

The three VHP-based CHARM intervention sessions were to be completed within a three month timeframe for all intervention arm participants. Most men recruited from CHARM communities (91.3 %) received Session 1 of CHARM; 77.2 % received Session 2, and 52.5 % received the couple’s session with their wife. Follow-up survey assessments were conducted at 9&18 months post-baseline with couples from both comparison and treatment clusters using the same procedures described above for baseline data collection; no additional referrals were provided at these time points unless requested. Additionally, at 18 month follow-up, wives were tested for pregnancy; pregnancy tests were obtained at only two time points to reduce costs and burden for interviewers. Also at 18 month follow-up, a subsample of couples (two couples per intervention village) were randomly selected to participate in in-depth interviews subsequent to their surveys; interviews assessed how the intervention affected the way the couple considers, discusses and uses family planning methods in their relationship. CHARM-trained VHPs (*n* = 16) participated in brief in-depth interviews subsequent to completion of the study to assess their perceptions of how the intervention affected family planning practices among rural young men and their wives. From March to December 2012, baseline data were collected. Subsequently, 9 month follow-up data collection was collected from November 2012 to September 2013, and 18 month follow-up surveys were collected 9 months after those dates. Of the 1081 couples participating in baseline assessment, 83.1 % (*n* = 898) and 82.4 % (891 couples) completed 9 and 18 month follow-ups, respectively [See Fig. 3. Consort Flowchart.].

